### Sample size estimate/power calculations

Statistical power analysis was conducted to estimate the sample size to test our hypothesis in G*Power (Version 3.1.9.4, Heinrich Heine University of Duesseldorf) (Faul et al., 2009). The following input parameters were used to obtain small-sized test × group interaction effects within an ANOVA: effect size (*f* = 0.15) (i.e., a small effect, (Tudor-Locke et al., 2011), type I error (α = 0.025), type II error (1-β = 0.8), number of groups (n = 4), number of measurements (n = 2), correlation between measurements (r = 0.60).

The size of the estimated sample to generate sufficient power to achieve the small effect is N = 88. To compensate for the estimated dropout rate of 30% (e.g., 20% lost to follow-up; plus 10% mortality) we plan to include a total of N = 116 participants. Based on the study design, we will integrate N = 29 participants in each condition.

Regarding the special cohort, recruiting approximately 30 participants per intervention arm per nursing home seems unrealistic, so multiple nursing homes will be needed for each intervention arm. As the number of nursing homes is also limited, each one needs to take on more than one intervention arm to reach a total of ∼30 participants. By the life expectancy of the special cohort and for ethical reasons, we have limited the maximum study duration to 1 year per participant. This means that each participant can complete two intervention phases and one follow-up phase per year, nested in a nursing home. In terms of the four intervention arms, this means six different possible combinations (this means six different nursing homes), each with 10–20 nursing home residents participating in the study.

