#### Physical functioning

The Short Physical Performance Battery (SPPB) (Guralnik et al., 1994) assesses lower-extremity function via balance, gait speed, and sit-to-stand performance. Balances will be tested across three progressively challenging stances (parallel (0–1 point), semi-tandem (0–1 point), and tandem stand (0–2 points); balance sum 0–4 points). To get into the specified position, participants will be allowed to hold on to an aid; however, aids are not allowed during the measurement. Gait speed will be recorded over 4 m at a comfortable pace, with an aid being used if necessary (0–4 points). Leg strength will be measured by the time taken to complete five chair rises (0–4 points). Individual scores will be summed up to a total from 0 (low mobility/functionality) to 12 points (full mobility/functionality). A change of ∼1.0–1.3 points is considered clinically meaningful (Guralnik et al., 1994).

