### Statistical analysis

The descriptive statistics will be presented as either group mean values and standard deviations/errors or medians and interquartile ranges, depending on the distribution of the outcome measures. The intervention effect for the primary outcomes (Number of Steps and SPPB) will be analyzed separately using a 4 (between group: PA-promoting culture intervention, guided environmental intervention, non-guided environmental intervention, or exercise intervention) × 2 (within test time point: t1:t2, and t2:t3) linear mixed model, where participants can be nested within nursing homes and be calculated as a random effect. The Follow-Up effects will be analyzed additionally using a 4 (between group: all interventions) x 3 (within test timepoint: t1/t2 – t2/t3 – t4). If baseline differences are found, the baseline assessment values, as well as age and sex discrepancies, will be included as covariates in the statistical model. In cases of statistically significant interaction effects, Bonferroni-adjusted *post hoc* tests (such as t-tests or Wilcoxon tests) will be employed to identify significant differences between groups from baseline to post-allocation testing. The data will be pre-processed and analysed using SPSS.

The effect size will be determined using Cohen’s f, which indicates the magnitude of treatment effectiveness and helps assess whether a statistically significant difference is practically significant (Cohen and Ebl, 1988). Cohen’s f values are classified as small (0 ≤ f ≤ 0.24), medium (0.25 ≤ f ≤ 0.39), or large (f ≥ 0.40) (Grissom and Kim, 2011). For *post hoc* analysis, Cohen’s d effect size will be calculated. Additionally, PSdep scores (probability of superiority for dependent samples) will be calculated as an estimate of effect size in non-parametric *post hoc* tests. The significance level will be set at p < 0.05. An intention-to-treat analysis will be conducted, considering all participants in the groups to which they were randomly assigned, regardless of whether they received or adhered to the assigned intervention. We will control participation in the interventions to analyze the effect of the intervention in more detail. Multiple imputations will be used to handle missing data, assuming that the missingness is random. If more than 40% of participants are lost to outcome assessment or demonstrate insufficient participation in training sessions, an additional per-protocol analysis will be conducted.

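### The sample-size paragraph claims 80% power at N = 88 for a small effect without stating the scale of f; in the ANOVA it describes, neither reading of f gives that power, and the default reading implies arms 0.60–0.85 SD apart

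*Protocol article*

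**What the plan says.** The section Sample size estimate/power calculations describes a G*Power calculation: "The following input parameters were used to obtain small-sized test × group interaction effects within an ANOVA: effect size (*f* = 0.15"). The other inputs are "type I error (α = 0.025"), "type II error (1-β = 0.8"), four groups, two measurements and a correlation of 0.60 between measurements. The result is given as: "The size of the estimated sample to generate sufficient power to achieve the small effect is N = 88". This is raised to 116 for an expected 30% dropout, and the note to Figure 1 rounds 116 to 120.

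The Statistical analysis section plans a 4 (group) × 2 (time) linear mixed model for each primary outcome, run in SPSS. It plans to use Cohen's f to judge practical significance, with these bands: "Cohen’s f values are classified as small (0 ≤ f ≤ 0.24), medium (0.25 ≤ f ≤ 0.39), or large (f ≥ 0.40").

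Neither section says whether f is standardised by the SD at one occasion or by the SD of change. Neither expresses the assumed effect in steps per day or SPPB points. The Physical functioning section does give a threshold in points ("A change of ∼1.0–1.3 points is considered clinically meaningful"), but the sample-size section does not use it.

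**The concern.** With two time points, a group × time interaction is a comparison of mean change across four arms. When G*Power takes a correlation between measurements as an input, its default f is defined against the single-occasion SD, and the program converts it to the change scale internally. A small number on the input scale can therefore stand for a considerably larger effect on the scale actually tested.

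Two things are at stake. The first is the size of effect the trial was planned around: a reader who sees the small-effect label will picture smaller differences between arms than the inputs imply. The second is the power claim, which is a stated figure that can be checked against the listed inputs.

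**Working it through.** **Inputs (Sample size estimate/power calculations).** f = 0.15, α = 0.025, target power 0.80, k = 4 groups, m = 2 measurements, r = 0.60, stated N = 88. The bands for f come from the Statistical analysis section.

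**Step 1. The plan's own figure, default scale.** The within-between interaction uses a noncentral F with df1 = (k − 1)(m − 1) = 3, df2 = (N − k)(m − 1) = N − 4, and

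λ = N·f²·m/(1 − r) = N × 0.0225 × 2/0.4 = 0.1125·N.

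| N analysed | λ | Power at α = 0.025 |
|---|---|---|
| 88 | 9.90 | 63% |
| 116 | 13.05 | 78% |
| 120 | 13.50 | 80% |

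The stated inputs require 120, not 88. At α = 0.05, 88 still gives only 73%, and 104 are needed with equal groups. N = 88 does appear if one element is changed: two groups instead of four, four measurements instead of two, or the time main effect instead of the interaction. The protocol does not show which of these, if any, occurred. The 78% at 116 assumes that all 116 are analysed. After the protocol's own 30% loss, 116 × 0.70 = 81 remain, and power is 58%.

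**Step 2. The same f on the change scale.**

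f(change) = f·√(m/(1 − r)) = 0.15 × √5 = 0.335; partial η² = 0.1125/1.1125 = 0.101.

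By the protocol's bands, 0.15 is small and 0.335 is medium.

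**Step 3. The difference between arms in outcome SDs.** With two occasions, the interaction cell effects are ±δ/2, where δ is an arm's deviation in mean change. The SD of the four arm mean changes is therefore 2 × 0.15 = 0.30 outcome SD. The distance between the best and worst arms depends on the pattern of means:

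- two arms high, two low: 2 × 0.30 = 0.60 SD
- equally spaced: 2√(9/5) × 0.30 = 0.80 SD
- two extremes, two in the middle: √8 × 0.30 = 0.85 SD

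This range follows from f alone. Only the 0.335 depends on r. A simulation of change scores with 22 per arm gave power of 64% for the 0.60 SD pattern and 63% for the 0.85 SD pattern, in line with Step 1.

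**Step 4. The alternative reading, f = 0.15 already on the change scale.** Here λ = N·f² = 0.0225·N. At N = 88, λ = 1.98 and power is 12%. At 116, λ = 2.61 and power is 16%. Reaching 80% takes about 579 (λ = 13.03).

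**The case against.** The strongest reply is that nothing here is contradictory. f = 0.15 is a legitimate input under G*Power's default definition, it lies inside the protocol's small band on that scale, and the bands are not said to apply to change scores. That stands. A reader might infer that the small label is simply false, or that power for a small effect does not exist at all. The documents do not support this: the label depends on a scale that is not disclosed. For the same reason, 12% and 579 apply only if f was meant on the change scale, and should not be set against the default-scale calculation as though both held together.

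A second reply is that the trial is a crossover. Each resident contributes two intervention phases, whereas the ANOVA in the sample-size section uses one change per resident. This also stands. A generalised-least-squares calculation with both periods (compound symmetry, r = 0.60, α = 0.025, period effects, no clustering, no carryover) gives a median power of about 95% at 88 for f = 0.15 on the default scale, and about 85% in the least favourable ordering. Those assumptions are optimistic, and clustering by home and carryover would pull the figure down. It still means that the Step 1 figures cannot be called upper limits on the trial's power.

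A third reply concerns SPPB. A reader might infer that the trial is underpowered for the 1.0–1.3 point threshold. The documents give no SPPB SD, and the threshold is worded as a change, not as a difference in mean change between the best and worst of four arms. No power figure in SPPB points can be derived from the document alone. Nor does it say how a non-significant interaction would be interpreted.

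These replies leave two things untouched: the 80% attached to N = 88 does not follow from the listed inputs, and the assumed effect is not identifiable from the text.

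**Conclusion.** The point holds as a misstatement of power and an undisclosed effect scale. In the one-comparison ANOVA that the section describes, 80% power at N = 88 is not delivered on either reading of f: 63% on the default scale (120 needed) or 12% on the change scale (about 579 needed). On the default scale, the planned effect is a 0.60–0.85 SD difference in mean change between extreme arms. If the interaction effect is later reported as a partial f, the effect planned as small would appear as 0.34 and be classed as medium.

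This rests on the stated inputs, equal arms and independent residents. Clustering and the second period are left out, as in the protocol's own calculation, and they act in opposite directions, so these figures bound the trial's actual power in neither direction.

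**What to change.** In Sample size estimate/power calculations:

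1. State the scale on which f = 0.15 is defined.
2. If it is G*Power's default, replace the small-effect wording with what it implies: a difference in mean change of 0.60–0.85 SD between the most and least effective arms, equivalent to f = 0.34 on the change scale at r = 0.60.
3. Replace 80% power at 88 with 63% at 88, 78% at 116 and 80% at 120 analysed. If a different test or input was intended, state it and rerun.
4. Give the effect in steps per day and in SPPB points, with the SDs the team assumes.

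In Statistical analysis, name the scale of the reported Cohen's f and use that same scale when applying the bands to the results.

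The cost is one recalculation and a few sentences. The stated power and detectable effect become less favourable. No extra recruitment and no change to conduct is involved.

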**FIGURE 1 F1:**
[figure not shown]
Study design- CONSORT Flow-Diagram of the PROGRESS project. Note: The power calculation determined that a total of 116 participants were required. To improve traceability, this number has been rounded up to 120.

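### The stated N = 88 cannot be reproduced from the printed inputs, which need 120 analysed, and the 30% dropout allowance does not retain even 88

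*Protocol article*

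**What the plan says.** The section on sample size and power says the calculation was done in "G*Power (Version 3.1.9.4, Heinrich Heine University of Duesseldorf"), and that the "input parameters were used to obtain small-sized test × group interaction effects within an ANOVA". The effect size is f = 0.15, described as "i.e., a small effect". The other inputs are "type I error (α = 0.025"), power 0.8, and "number of groups (n = 4), number of measurements (n = 2), correlation between measurements (r = 0.60"). The result is given as: "The size of the estimated sample to generate sufficient power to achieve the small effect is N = 88".

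To cover an expected 30% dropout (20% lost to follow-up plus 10% mortality), the section continues: "we plan to include a total of N = 116 participants", that is, 29 in each condition. The note to Figure 1 repeats the enrolled figure ("The power calculation determined that a total of 116 participants were required") and says it was rounded up to 120. The abstract gives a target of at least 120, and the section on recruiting nursing homes again uses 116 and 29 per arm.

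**The concern.** All the inputs for a standard calculation are printed, so the output can be checked. An interaction of four groups with two time points has three numerator degrees of freedom, and 88 is too small for it at this effect size and α. The step from 88 to 116 also looks like adding 30% to the target, not dividing by the proportion retained.

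The stated 80% is what readers will use to interpret a null result. The hypotheses are that some interventions do better than others, and the Statistical analysis section makes the post hoc comparisons depend on a significant interaction. If the printed inputs do not give 80% for that interaction, a non-significant result would be read as stronger evidence of no difference than it is.

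**Working it through.** **Inputs**, all from the sample size section: f = 0.15; α = 0.025; power 0.80; k = 4 groups; m = 2 measurements; ρ = 0.60; stated N = 88; dropout 30%; enrolled 116. The target of 120 comes from the abstract and the Figure 1 note.

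**Formula.** G*Power's repeated-measures ANOVA, within-between interaction, with ε = 1:

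- λ = f²·N·m/(1 − ρ) = 0.0225 × N × 2/0.40 = 0.1125·N
- df1 = (k − 1)(m − 1) = 3; df2 = (N − k)(m − 1) = N − 4
- power = P(F(df1, df2, λ) > F critical at α)

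**Step 1: try to reproduce 88.**

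| N analysed | λ | Power, α = 0.025 | Power, α = 0.05 |
|---|---|---|---|
| 81 | 9.11 | 58.4% | 69.3% |
| 84 | 9.45 | 60.5% | 71.1% |
| 88 | 9.90 | 63.1% | 73.5% |
| 116 | 13.05 | 78.5% | 85.9% |
| 119 | 13.39 | 79.8% | 86.9% |
| 120 | 13.50 | 80.2% | 87.2% |

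The stated figure is not reproduced: 80% is first reached at N = 120. A 20,000-run simulation of the four-group F test on change scores gave 63.4% at 88 and 80.1% at 120. A more lenient α does not explain the gap, because at α = 0.05 the smallest N is still 101.

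**Step 2: what does give 88?** With the other printed values unchanged:

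- time main effect (df1 = 1), four groups: 79.9% at 87, 80.4% at 88
- interaction with two groups (df1 = 1): just under 80.0% at 87, 80.5% at 88
- interaction with four groups and four measurements, in steps of four: 79.8% at 84, 82.3% at 88

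Three different settings lead to 88. None is the calculation described.

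**Step 3: dropout.**

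- As apparently applied: 88 × 1.3 = 114.4, and the next multiple of four is 116 = 4 × 29
- To retain 88: 88/0.7 = 125.7, so 126
- As successive losses of 20% and 10%: 88/(0.8 × 0.9) = 122.2, also above 116
- Retained from 116: 116 × 0.7 = 81.2, so 81
- Retained from 120: 120 × 0.7 = 84
- Loss that 116 can absorb while keeping 88: 28/116 = 24%

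**Step 4: both together.** The first two rows of the table give 58.4% power with 81 and 60.5% with 84. Solving the same formula for f at 80% power gives 0.184 with 81 and 0.181 with 84. For the printed inputs, the enrolment that retains 120 after 30% loss is 120/0.7 = 171.4, so 172 (43 per condition).

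**The case against.** Four points can be made for the plan.

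- **The formula is not the design.** Each resident receives two interventions, and each intervention is paired once with each of the others, so it runs in three of the six homes. With 116 residents, about 58 receive each intervention, not 29. Counting 81 completers twice gives 162 records and 92% on the same formula. That figure is not valid either, because the records are correlated within residents and homes. This objection stands: 58% to 60% does not bound the trial's power in either direction. It does not rescue 88, which the protocol presents as the output of the four-group ANOVA.
- **The 30% may overstate loss for the primary test.** No time point is attached to it. The study runs to 52 weeks, but the primary model uses t1 to t3, and multiple imputation under intention to treat is planned. With 20% loss from 116, about 93 remain and power on the same formula is 66%. This stands as a caution about size. The plan itself nevertheless sets 30% as the loss to cover, and 116 does not cover it.
- **The target is 120, the number the inputs require.** This is a coincidence. Here 120 is an enrolment figure, reached by rounding 116, and 84 remain after the planned loss.
- **Little changes in practice.** Recruitment of homes has ended and no analysis changes. That is so, but the power claim remains in print.

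A reader might also infer that the authors sized the wrong test. The document does not establish this, because a misprinted number of measurements would explain 88 equally well.

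**Conclusion.** Two statements in the sample size section are wrong as written. The printed inputs need 120 analysed, not 88, for the stated interaction. An enrolment of 116, or of 120, does not retain 88 after the plan's own 30% loss. Taken together, the plan's own calculation gives about 58% to 60% power at f = 0.15 where 80% is claimed, or 80% power at f of about 0.18.

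The figure of 120 rests only on the printed inputs and G*Power's formula with ε = 1. The power range also assumes that the full 30% is lost to the primary test and that the four conditions are independent parallel groups.

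Two stronger readings are not supported. The first is that the trial's real power is 58%: the planned analysis is a mixed model on a clustered crossover, and this formula describes neither feature. The second is that 172 residents must be recruited: 172 is only the enrolment that the printed inputs imply under the parallel-group formula.

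**What to change.** Correct the sample size paragraph, the Figure 1 note and the recruitment section so that they agree. There are two ways to do it:

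1. Supply the test and inputs that actually gave 88. If that test is not the test × group interaction, say so. Correct the dropout step in any case (88/0.7 = 126).
2. Keep the printed inputs and state that they need 120 analysed, or 172 enrolled at 30% loss. State that the planned 116 to 120 leaves 81 to 84, with about 58% to 60% power at f = 0.15, or 80% at f of about 0.18.

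In either case, label the figures as coming from an ANOVA with four parallel groups that allows neither for each resident receiving two interventions nor for clustering in six homes, so that they are not read as the power of the planned mixed model.

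No extra residents and no change to the design or analysis are required. The cost is a revised paragraph with a less favourable stated power.

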**Methods:**

The study employs a cluster-randomized controlled crossover design with four intervention groups. Participants will be randomly assigned to one of four groups: a combined exercise and guided environmental intervention (physical activity-promoting culture), an exercise intervention, a guided environmental intervention, or a non-guided environmental intervention. The exercise intervention involves group-based sessions twice a week, while the environmental intervention focuses on implementing PA into daily routines. The guided environmental intervention is equivalent to the non-guided one but provides additional support two to four times weekly. We aim to recruit at least 120 participants from six nursing homes. Each facility will receive two interventions in a 16-week crossover design (36 weeks in total, including weeks for measurements), followed by a 16-week non-guided environmental intervention (follow-up phase). Primary outcomes include steps per day as an indicator of PA behavior, and the Short Physical Performance Battery (SPPB) to assess physical functioning.

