#### Recruitment of nursing homes

The study has aimed to identify at least six nursing homes around Münster, Germany, that are willing to take part. To ensure enough participants, institutions were selected based on their number of residents (ideally >100), as we aimed to recruit 10–20 participants per nursing home (n = 116) and 29 per intervention arm (see power calculation). The first point of contact was with the nursing home management via email or telephone. During this initial contact, the possibility of participating in a study to promote physical activity was enquired about, without providing any details. Participation is voluntary and not remunerated. Nursing home recruitment ended in the third quarter of 2023.

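### The 29 residents per condition and the 80% power belong to a four-group parallel design, not to this six-home crossover, which gives 58–60 residents per intervention

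*Protocol article*

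**What the plan says.** The section *Sample size estimate/power calculations* targets "small-sized test × group interaction effects within an ANOVA". Its inputs are f = 0.15, α = 0.025, power 0.80, four groups, two measurements and a correlation of 0.60. It reports N = 88, allows for 30% dropout, arrives at 116, and concludes: "Based on the study design, we will integrate N = 29 participants in each condition". The section *Recruitment of nursing homes* repeats the figure: "as we aimed to recruit 10–20 participants per nursing home (n = 116) and 29 per intervention arm".

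The design is described differently elsewhere. The Abstract says: "Each facility will receive two interventions in a 16-week crossover design". The section *Trial design* says that the six possible pairs of interventions are randomised to the homes, so that each intervention is paired once with each of the other three. The sample size section itself says that each resident can complete two intervention phases, and that homes are limited in number, so "each one needs to take on more than one intervention arm to reach a total of ∼30 participants".

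The total is stable throughout: at least 120 in the Abstract, 116 rounded up to 120 in the note to Figure 1, and 116 in the two sections above. The section *Statistical analysis* plans a linear mixed model that allows residents to be nested within homes as a random effect.

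**The concern.** Dividing 116 by four is correct only if each resident sits in exactly one arm. Here each resident contributes to two. The feasibility argument in the same section reaches about 30 per intervention by letting each home, and hence each resident, serve more than one intervention. The two figures of about 30 therefore look alike but count residents in different ways.

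The power calculation has the same problem. It treats residents as independent members of four separate groups. The trial randomises six homes, measures each resident under two interventions, and plans a model with a home level. Neither the gain from the crossover nor the loss from clustering enters the listed inputs. A reader who takes 80% as the chance of detecting f = 0.15 on steps per day or the Short Physical Performance Battery is relying on a figure for another design.

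**Working it through.** **1. The plan's own figure.** For a within-between interaction, λ = f²·N·m/(1 − r), with (k − 1)(m − 1) and (N − k)(m − 1) degrees of freedom. With f = 0.15, m = 2, r = 0.60, k = 4 and N = 88:

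- λ = 0.0225 × 88 × 2 / 0.40 = 9.9 on 3 and 84 df.
- The critical F at α = 0.025 is 3.28, and power is about 63%.
- 80% power needs N = 120 (λ = 13.5).

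So 88 is not reproduced for the stated test. It does appear for other tests, for example the time main effect with the same inputs. This is a separate matter, but it means that 80% does not follow at N = 88 even for the parallel design.

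The step from 88 to 116 matches 88 × 1.30 = 114.4, rounded up to a multiple of four. Then 116/4 = 29. The power was thus computed at 22 per group (88/4), and 29 is the figure after the dropout allowance.

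**2. Counting residents per intervention.** Four interventions form six pairs, so each intervention runs in three of the six homes.

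| Unique residents | Per home | Per intervention (residents × 2 / 4) |
|---|---|---|
| 88 | 14.7 | 44 |
| 116 | 19.3 | 58 |
| 120 | 20 | 60 |

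Read backwards, 29 per intervention under the crossover would need only 29 × 4 / 2 = 58 residents. The reasoning that reaches about 30 corresponds to 10 residents in each of three homes (3 × 10 = 30). The planned total corresponds to about 20 in each (3 × 20 = 60).

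**3. Illustrative power for the actual design.** These inputs are assumed:

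- Effects of +0.42 SD for the combined intervention, −0.42 SD for the non-guided one and 0 for the other two. Their root mean square is √(2 × 0.42² / 4) ≈ 0.30, which is f = 0.15 on the interaction scale.
- r = 0.60, α = 0.025, 20 analysed per home and no carry-over.
- Home-by-phase variance as a share of total variance. The protocol states no value.

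The method is generalised least squares on the 12 home-by-phase means, with power from the noncentral F averaged over the 64 possible orders. Error df are 12 − 1 (intercept) − 1 (phase) − 3 (interventions) = 7. The range covers two readings of the outcome: post-phase values, or change scores with t2 shared between phases.

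| Home-by-phase variance | Power, 7 df |
|---|---|
| 0% | about 82–88% |
| 1% | about 63–74% |
| 5% | about 27–39% |

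A rerun of this calculation agreed to within about two percentage points. If a resident's two change scores are taken as uncorrelated, the 0% figure is about 76%.

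**4. Second check, after dropout.** This uses 88 analysed, equally spaced effects matched to f = 0.15, and an assumed intracluster correlation of the change score.

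| ICC of change | 7 error df | About 80 error df (resident level) |
|---|---|---|
| 0 | 60–69% | 89–94% |
| 0.01 | 54–59% | 84–89% |
| 0.05 | 36–41% | 65–70% |
| 0.10 | 25–31% | 47–57% |

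The answer therefore turns on the home-level correlation and on how the model assigns degrees of freedom. The protocol's power statement uses neither.

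**The case against.** The strongest reply is that the design may do better than stated. Each resident supplies two interventions, which doubles the exposures, and the planned mixed model can use the within-resident comparison. With negligible home-level variance the checks do exceed 80%, including with 7 df and an estimated variance at 20 analysed per home. That stands: the documents do not fix the direction of the error. A reader might infer that the trial is underpowered, but the protocol supports only the statement that 80% was not derived for this design.

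Three other stronger readings are tempting and should not be drawn:

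- **A recruitment target that could be 60 or 116.** A reader might multiply the lower end of 10–20 per home by six. No section sets 60 as a target, and every stated total is 116 or 120. The fault lies in the per-intervention figure and in the reasoning behind about 30.
- **Only 2 error degrees of freedom.** Fixed home effects on the 12 home-by-phase means would leave 12 − 6 − 1 − 3 = 2, with a critical F of 39.2. The protocol does not plan that analysis. Its mixed model has a random effect with residents nested in homes.
- **The usual parallel-cluster design effect.** It applies when each home receives one intervention, so it would ignore the crossover just as the protocol's calculation does.

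It is also fair that recruitment of homes ended in the third quarter of 2023, so the number of homes is settled. That bears on severity but does not make the stated figures right.

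**Conclusion.** The point holds. The figure of 29 per condition is wrong for this design. With 116–120 residents, each intervention is received by 58–60 across three homes. This follows by counting alone and needs no assumption beyond the design as described and before dropout.

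The 80% power is not a property of the trial as designed. Its true value depends on a home-level correlation that the power statement does not give. Under the assumptions above it runs from about 82–88% with no home-by-phase variance to about 27–39% when that variance is 5% of the total, at 20 analysed per home and 7 error df. It is lower after dropout and higher if resident-level degrees of freedom are used. These percentages are illustrative and should not be quoted as the trial's power. Severity is should-fix: both primary outcomes are affected, but the remedy is a restatement and does not change the design.

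**What to change.** 1. Keep the target of 116–120 unique residents and state it as about 20 per home in six homes.
2. In the sections *Recruitment of nursing homes* and *Sample size estimate/power calculations*, replace 29 per arm or condition with 58–60 per intervention, received across three homes. Reword the argument that leads to about 30 so that it counts residents in the same way.
3. Replace the ANOVA power statement with a simulation under the planned mixed model: six homes, six ordered pairs, residents measured under two interventions, t2 shared between phases, and the 30% dropout. Run it over a stated range of home and home-by-phase correlation, and state the method for degrees of freedom.
4. Report the resulting power, or the detectable effect, for each primary outcome. If power is below 80% over a plausible part of the range, say so, and say that conclusions will rest on estimates with confidence intervals.

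The cost is about half a day of simulation and a few restated figures. No extra homes or residents are needed.
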